### Data analysis

Intention-to-treat (ITT) analysis will be performed. The full analysis set (FAS) will include all randomized patients who took the study drugs at least once and had at least 1 primary or secondary efficacy evaluation after baseline. For assessment of missing primary efficacy variables, the last observation carried forward (LOCF) technique will be used. The per-protocol set (PPS) will include ITT patients completing at least 22 weeks of treatment, and those who discontinued the study due to a poor therapeutic response (FPG >13.3 mmol/L [240 mg/dL]) after 12 weeks of treatment, provided they have no major protocol deviations and had a valid assessment of HbA1c levels within 7 days after their last dose of study drug. Any major deviation from the protocol will be identified and documented in the analysis plan. Patients will be analyzed in the treatment group to which they were randomly assigned for the efficacy assessment.

The safety analysis set (SAS) will include patients who took the study drugs at least once and had at least 1 safety assessment after baseline. The safety analyses will be according to the patients’ treatment, and will include the description of any AEs.

The FAS set will be used as the primary population for the primary efficacy variable, the change from baseline in HbA1c levels at 24 weeks. The primary efficacy variable will be analyzed using an analysis of covariance (ANCOVA) model and the LOCF approach.

Non-inferiority of the study drug will be analyzed using the null hypothesis and a unilateral alternative hypothesis, which are defined as follows:

$$H_{0},\delta_{\mathrm{vildagliptin}}\geq \delta_{\mathrm{metformin}}+0.3\%$$

$$H_{a},\delta_{\mathrm{vildagliptin}}<\delta_{\mathrm{metformin}}+0.3\%$$

where δ represents the change from baseline.

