In order to control the overall type I error at alpha = 0.05, a sequential test procedure along with the Hochberg procedure will be employed. Non-inferiority testing for the overall population will be performed first. After achieving non-inferiority for the overall population, non-inferiority testing for the 4 subgroups will then be performed. Secondary efficacy variables include percentages of patients achieving therapeutic goals at the study endpoint: HbA1c ≤6.5%, HbA1c ≤6.5% without GI side effects, and absolute decreases in HbA1c from baseline of ≥1%, ≥0.7%, and ≥0.5%. In the FAS and PPS populations, the percentages of patients achieving the therapeutic goals will be analyzed and compared between treatment groups using the Chi-square test.

To assess the robustness of the results of the primary efficacy analysis, i.e., the change from baseline in HbA1c at 24 weeks, an ANCOVA model with LOCF will be used for the PPS. For the primary and secondary efficacy endpoints, subgroup analyses based on age and BMI will be performed.

Safety analyses will include summaries of AEs, changes from baseline in vital signs, the number of subjects with post-baseline laboratory values that will fall outside predetermined ranges, and the frequency and severity of hypoglycemic events. Adverse events will be summarized by system organ class and preferred terms. Summaries of AEs by severity and by relationship to study drug will also be provided.

The incidence of patients with any GI events will be compared between treatment groups using Fisher’s exact test.

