### Sample size estimations

Non-inferiority testing will be performed on the subgroups of patients based on age and BMI. Assuming a treatment group difference of 0, standard deviation of 1, and a non-inferiority margin of 0.5, 690 patients will provide 90% power at a 1-sided with significance level of 0.05. Allowing for a 20% dropout rate, the number of subjects required for randomization is 690/ (1+20%) = 828 patients, yielding a total of 4 × 828 = 3312 subjects. For the estimation of the sample size, nQuery Advisor®, version 7.0, will be used.

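### Overall non-inferiority is decided on the FAS with LOCF alone; the planned PPS analysis cannot change that decision, and no rule covers disagreement

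*Protocol article*

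**What the plan says.** All of this is in the protocol article.

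- **Primary population and method (Data analysis).** "The FAS set will be used as the primary population for the primary efficacy variable". The variable is the 24-week HbA1c change, and the method is ANCOVA with missing values filled by LOCF. The hypotheses that follow use a margin of 0.3% HbA1c. The overall population is tested first, and the four age/BMI subgroups only after the overall test succeeds.
- **Role of the PPS (Data analysis).** Its stated purpose is "To assess the robustness of the results of the primary efficacy analysis". The method is the same as for the FAS: "an ANCOVA model with LOCF will be used for the PPS". No sentence makes this result a condition of the claim or says what follows if the two sets disagree.
- **PPS membership (Data analysis).** "The per-protocol set (PPS) will include ITT patients completing at least 22 weeks of treatment". It also takes in poor-response discontinuations after week 12. Major protocol deviations are excluded, and an HbA1c within 7 days of the last dose is required.
- **FAS membership (Data analysis).** A treated, randomised patient enters with one post-baseline value of any primary or secondary efficacy variable.
- **Schedule (Table 3).** HbA1c is measured at weeks −4, 0, 12 and 24, and FPG also at week 4. Note a calls for the visit 5 assessments at early withdrawal.
- **Dropout (Sample size estimations).** "Allowing for a 20% dropout rate".

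**The concern.** In a superiority trial, values that carry little treatment difference work against the claim. In a non-inferiority trial they work for it, because they pull the estimate toward 0 and away from the margin.

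Three features of this design make such values plausible:

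- FPG is a secondary efficacy variable, so a week-4 FPG alone admits a patient to the FAS. The first scheduled post-baseline HbA1c is at week 12. If such a patient leaves and no withdrawal HbA1c is taken, the only value to carry forward is baseline, which is a change of zero.
- Under Study design, Group B takes metformin 500 mg tid from visit 2 and 1000 mg bid only from visit 3. An HbA1c measured before visit 3 cannot reflect the high-dose comparator named in the primary objective.
- The text below Table 2 stops treatment in patients who cannot tolerate the GI symptoms of the visit 2 dose increase. Only Group B has its metformin raised at that visit, so early stopping could fall more on the comparator.

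At stake is the primary claim and, through the test order, access to the subgroup tests. The analysis best placed to show dilution is already planned but has no say in the decision.

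**Working it through.** **Inputs from the article.** N = 3312 at 5:1, so 2760 and 552. SD 1, one-sided alpha 0.05, 20% dropout. Margin 0.3 from the hypotheses.

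**Which margin.** Sample size estimations states a margin of 0.5, so I first checked which margin gives its 690 per subgroup. Control n = (1 + 1/5) × (1.645 + 1.282)² / margin².

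- Margin 0.5: 42 control patients, 252 in total. This does not reproduce 690.
- Margin 0.3: 115 control patients, 690 in total. This is an exact match.

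I therefore use 0.3 throughout. The 0.5 is a separate inconsistency.

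**Assumptions not in the article.** The true difference is exactly 0.3 in patients who stay on treatment. A share f of FAS values is carried forward and keeps a fraction k of that difference. All 3312 patients are in the FAS and the SD is unchanged.

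**False-claim rate of the overall FAS test.**

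- SE = √(1/2760 + 1/552) = 0.0466
- Expected FAS difference = 0.3 × (1 − f + f·k)
- Rate = Φ((0.3 − expected difference)/SE − 1.645)

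| f | k = 0: difference | rate | k = 0.5: difference | rate |
|---|---|---|---|---|
| 0% | 0.300 | 5.0% | 0.300 | 5.0% |
| 5% | 0.285 | 9.3% | 0.2925 | 6.9% |
| 10% | 0.270 | 15.8% | 0.285 | 9.3% |
| 15% | 0.255 | 24.8% | 0.2775 | 12.3% |
| 20% | 0.240 | 36.0% | 0.270 | 15.8% |

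**How far past the margin this reaches.** With f = 20% and k = 0, a true difference of 0.325 gives 21.6%, 0.35 gives 11.2% and 0.375 gives 5.0%. The last follows because 0.8 × 0.375 = 0.30.

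**Effect of requiring both sets.** In a simulation of 200,000 trials at a true difference of 0.3 (f = 20%, k = 0, PPS = the remaining 80%), the overall FAS test passed in 36.2%, the PPS test in 4.9%, and both in 4.9%. This assumes that the PPS difference is undiluted and unbiased.

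**Power cost at a true difference of 0.**

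- Overall, PPS = 0.8 × 3312 ≈ 2650: SE = 0.0521, and Φ(0.3/0.0521 − 1.645) = 0.99998.
- Per subgroup, FAS of 828 (690:138): SE = 0.0933, power about 0.942.
- Per subgroup, PPS = 0.8 × 828 ≈ 662: SE = 0.1043, power 0.891.
- All four subgroups passing (Hochberg rejects all four when the largest p-value is at most 0.05): 0.942⁴ ≈ 0.79 on the FAS alone, and at most 0.891⁴ ≈ 0.63 if the PPS must pass too.

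**The case against.** The strongest reply is that a FAS-primary analysis with a supportive PPS is a legitimate design choice. The same ANCOVA is planned on the PPS, so a discordant result would be seen. The article is condensed, and a rule for disagreement might sit in the analysis plan. The first two statements are true, but seeing a discordance is not a rule for acting on it. Nor is this only silence: the article names the deciding analysis and gives the PPS a different purpose.

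A reader might infer that carried-forward values by themselves produce a false claim, or that the test's type I error is 36%. The documents support neither.

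- Table 3, note a, calls for an HbA1c at early withdrawal. Where that visit happens, the carried value is measured on treatment. Patients leaving after week 12 should also have the week-12 value.
- Patients with no post-baseline efficacy value are outside the FAS, so not all of the 20% would be carried forward.
- The direction of LOCF bias is not given. If early losses fell more on the vildagliptin arm, it could work against the claim.
- The inflation needs a true difference at or just above 0.3, and it is measured against the effect in patients who stay on treatment. The article states its hypotheses for change from baseline, with the FAS primary.

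Two further objections stand. The PPS is selected after randomisation and drops patients who stop early for reasons such as GI intolerance, which may differ by arm, so it cannot replace the FAS. It is also analysed with LOCF, so the joint rule limits the problem without removing LOCF. Finally, extending the rule to every subgroup would have a real power cost.

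**Conclusion.** The point holds for the overall test. As written, FAS with LOCF alone decides, and the claim would formally stand with a PPS limit above 0.3%. Dilution toward the claim is plausible from the FAS entry rule, the HbA1c schedule and the Group B titration, and is lessened wherever the withdrawal visit supplies an HbA1c.

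The size is conditional. At a true difference of 0.3, the false-claim rate is about 7–9%, 9–16% or 16–36% for 5%, 10% or 20% carried forward. The top figure is the extreme, with every one of the 20% in the FAS and contributing no difference; even then the excess is gone by a true difference of about 0.375. The carried shares and retained differences are assumptions, so these figures illustrate sensitivity and do not estimate this trial's error rate.

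The documents do not support a joint requirement in the four subgroups as a costless step. This is a cheap improvement to the overall decision rule, not a fatal flaw.

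**What to change.** Add to Data analysis: overall non-inferiority is concluded only if the upper one-sided 95% confidence limit of the adjusted difference (vildagliptin arm minus metformin arm) is below 0.3% in both the FAS and the PPS. State that the PPS is added to the FAS and does not replace it, and that PPS results for the four subgroup tests are reported as supportive.

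Cost: one sentence or two, since the PPS ANCOVA is already planned. Power for the overall test remains above 99.9% at a true difference of 0 with 80% of patients in the PPS. Subgroup power is essentially unchanged, because the joint rule is not applied there.

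### The overall non-inferiority test uses a one-sided 0.05 level that only the subgroup sample size needs; one-sided 0.025 would halve the error at the 0.3% margin at little cost in power

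*Protocol article*

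**What the plan says.** All references are to the protocol article.

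- **Hypotheses (Data analysis).** Non-inferiority is tested "using the null hypothesis and a unilateral alternative hypothesis". The null is that the HbA1c change on vildagliptin add-on is worse than that on metformin by 0.3% or more.
- **Error control (Data analysis).** The sequential and Hochberg procedure is adopted "In order to control the overall type I error at alpha = 0.05". The side of this 0.05 is not given.
- **Order (Data analysis).** "Non-inferiority testing for the overall population will be performed first"; the four age and BMI subgroups follow only if it succeeds.
- **Sizing (Sample size estimations).** The calculation is for one subgroup: "Assuming a treatment group difference of 0, standard deviation of 1", and "690 patients will provide 90% power at a 1-sided with significance level of 0.05". The margin printed there is 0.5. The total is 4 × 828 = 3312 randomized.

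The overall test has no level or margin of its own, and no power is stated for it.

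**The concern.** A one-sided test at 0.05 declares non-inferiority when the upper limit of a two-sided 90% interval lies below the margin. The usual choice for a non-inferiority claim is one-sided 0.025, that is, a 95% interval. In the subgroups the more lenient level has a purpose, because it keeps the number per subgroup at 690. The overall test inherits the same level although it has four times the patients and half the standard error.

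The overall test carries the main conclusion and is the gate to every subgroup claim. A conclusion that rests on a 90% interval invites challenge. If the leniency buys no useful power there, the sponsor takes on that challenge for nothing.

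**Working it through.** **Inputs.** SD 1, true difference 0, one-sided 0.05, 90% power, 690 per subgroup and 3312 in total (Sample size estimations); margin 0.3 (Data analysis); allocation 5:1 (Study design). Normal approximation throughout; a deficit means that the add-on arm is worse.

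**Step 1: reproduce 690.** With 5:1 allocation the control group needs n = 1.2 × SD² × (z₁₋α + z₀.₉₀)² / margin².

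- Margin 0.3, one-sided 0.05: 1.2 × (1.645 + 1.282)² / 0.09 = 114.2, so 115 control and 575 add-on, 690 in total. This matches, with power 90.2%.
- Margin 0.5, one-sided 0.05: 1.2 × 8.564 / 0.25 = 41.1, so 42 + 210 = 252. This does not match.
- Margin 0.3, one-sided 0.025: 140.1, so 141 + 705 = 846. This does not match.

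Of these settings only a 0.3 margin at one-sided 0.05 gives 690. The level therefore does real work in the subgroups: at 690 and one-sided 0.025, power for one subgroup would be 83.6%.

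**Step 2: standard error of the overall test.** SE = √(1/n_control + 1/n_add-on).

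- All 3312 randomized (552 and 2760): SE = 0.0466.
- Evaluable total 4 × 690 = 2760 (460 and 2300): SE = 0.0511, half the subgroup value of 0.1021.

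**Step 3: probability of declaring non-inferiority at the 0.3 margin.** P = Φ((0.3 − d)/SE − z₁₋α), where d is the true deficit. Largest observed deficit that passes = 0.3 − z₁₋α × SE.

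| Analysed | One-sided level | d = 0 | d = 0.1 | d = 0.3 (at the margin) | Largest passing deficit |
|---|---|---|---|---|---|
| 3312 | 0.05 | >99.9% | 99.6% | 5% | 0.223 |
| 3312 | 0.025 | >99.9% | 99.0% | 2.5% | 0.209 |
| 2760 | 0.05 | >99.9% | 98.8% | 5% | 0.216 |
| 2760 | 0.025 | >99.9% | 97.5% | 2.5% | 0.200 |

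For example, with 2760 analysed, d = 0.1 and one-sided 0.025: Φ(0.2/0.0511 − 1.960) = Φ(1.956) = 97.5%.

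**Step 4: sensitivity to the SD.** If the SD were 1.2 (an assumption; the protocol gives only 1), the standard errors become 1.2 × 0.0466 = 0.0560 and 1.2 × 0.0511 = 0.0613. Power at one-sided 0.025 is then still 99.97% (3312) or 99.8% (2760) at d = 0. At d = 0.1 it falls from 97.3% to 94.7% (3312) or from 94.7% to 90.4% (2760).

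**Step 5: familywise error with a 0.025 gate and Hochberg 0.05 behind it.** If the overall null is true, any false claim, overall or subgroup, has to pass the gate first, so the risk is at most 0.025. If the overall null is false, only subgroup nulls can be falsely rejected, and Hochberg holds that risk at 0.05. The family stays at or below the stated 0.05.

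**The case against.** The strongest reply is that nothing here is miscalculated. A one-sided alternative, a one-sided 0.05 sizing level and an overall alpha of 0.05 agree with one another, and the document adopts no 0.025 convention for this phase 4 study. The change would also rarely matter. With 3312 patients the two levels disagree only for an observed deficit between 0.209 and 0.223. At the planned difference of zero, 0.209 is about 4.5 standard errors away (0.209/0.0466). The subgroup claims would stay at 0.05 in any case. All of this stands, and it limits the weight of the point. It does not supply a reason for the lenient level in the overall test.

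Three stronger readings are tempting, and the documents support none of them.

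- A reader might infer an inflated error rate, because a true deficit of 0.2 would be declared non-inferior 69% of the time with 3312 patients, or 62% with 2760. A deficit of 0.2 lies inside the protocol's alternative, so that declaration is correct under its hypotheses. The figure comes mainly from the margin and the sample size; at one-sided 0.025 it is still 57% or 50%.
- A reader might infer that the overall margin should be 0.2. No passage supports that value, and the justification of a margin is commonly left to the full protocol. It is also not free: with one-sided 0.025, power at a true deficit of 0.1 would be 57% (3312) or 50% (2760).
- A reader might infer that an inert add-on could pass. That depends on how much up-titration itself lowers HbA1c, which the document does not state.

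**Conclusion.** The point holds as a cheap improvement of low to moderate weight. The plan controls the error rate that it states. For the overall test, however, one-sided 0.05 doubles the false-positive risk at the margin relative to one-sided 0.025 (5% against 2.5%) for a gain of at most 1.3 percentage points of power at a true deficit of 0.1 (98.8% − 97.5%, with 2760 patients), and practically none at zero difference.

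This rests on SD 1, 5:1 allocation, the 0.3 margin and between 2760 and 3312 patients contributing to the primary analysis. With an assumed SD of 1.2 the gain at a deficit of 0.1 rises to about 4 points (94.7% − 90.4%, with 2760 patients).

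It also rests on reading the 0.05 in the Data analysis section as one-sided, in line with the unilateral alternative and the sizing level. If a two-sided 95% interval was always intended, the change becomes a clarification.

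The firm documentary error nearby is the margin: "a non-inferiority margin of 0.5, 690 patients will provide 90% power" cannot be right as printed, since 0.5 gives 252 patients and 0.3 gives 690.

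**What to change.** 1. State in the Data analysis section that overall non-inferiority is declared, and subgroup testing opened, only if the upper limit of the two-sided 95% confidence interval for the overall difference (add-on minus metformin) is below 0.3%, which is one-sided 0.025.
2. Keep the four subgroup tests at Hochberg 0.05 and say that this level is one-sided. The 690 per subgroup and its 90% power then stand.
3. Reconcile the 0.5 margin in the sample size section with the 0.3% in the hypotheses.

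**Cost.** A few sentences and no additional patients. The largest observed overall deficit that passes falls from about 0.22 to 0.21 with 3312 patients analysed, or to 0.20 with 2760. The loss of power at a true deficit of 0.1 is 0.6 to 1.3 percentage points under the protocol's SD of 1.

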	• To demonstrate that the change from baseline in HbA1c levels after 24 weeks of treatment with vildagliptin 50 mg bid as add-on therapy to metformin 500 mg bid is non-inferior to high-dose metformin
**2.**	**Secondary objectives:**
	• To demonstrate in predefined patient subgroups [based on body mass index (BMI <24 and ≥24 kg/m^2^) and age (<60 and ≥60 years)] that vildagliptin add-on therapy to metformin is non-inferior to high-dose metformin in the change from baseline in HbA1c levels
	• To determine the percentages of patients achieving the target HbA1c level of ≤6.5% in the two treatment arms of the overall population and in the predefined subgroups
	• To determine the percentages of patients achieving the target HbA1c level of ≤6.5% in the two treatment arms of the overall population and in the predefined subgroups
	• To determine the mean change from baseline to 24 weeks in fasting plasma glucose in the overall population and in the predefined subgroups
	• To determine the mean change from baseline to 24 weeks in 2-hour postprandial glucose in a subsample of 464 patients with type 2 diabetes mellitus
	• Safety analysis
**3.**	**Exploratory objectives:**
	• To determine the mean change from baseline to 24 weeks in body weight and lipid parameters in the overall population and in the predefined subgroups
	• To determine the change from baseline to 24 weeks in β-cell function in a subsample of 464 patients with type 2 diabetes mellitus

BMI: body mass index; HbA1c: glycated hemoglobin.

Treatment will also be discontinued if the patient cannot tolerate the GI symptoms associated with a dose increase at visit 2. If patients in Group B cannot tolerate the GI symptoms at visit 3, the dose of metformin can be decreased by one tablet (250 mg) until the GI symptoms improve. After that, the dose will be gradually increased over 1–2 weeks. The dose of the metformin in Group B will be at least 500 mg bid until week 12. After week 12 (visit 4), dose adjustments of metformin will not be allowed at any time. Adjustment of the vildagliptin dose will not be allowed throughout the study.

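### The per-protocol comparison of the HbA1c-plus-GI-tolerability goal leaves out patients who stopped early for GI intolerance, who have all failed it, and so is biased against vildagliptin

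*Protocol article*

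**What the plan says.** All references are to the Protocol article.

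- **Goals.** Data analysis lists the responder goals as "HbA1c ≤6.5%, HbA1c ≤6.5% without GI side effects, and absolute decreases in HbA1c from baseline of ≥1%, ≥0.7%, and ≥0.5" percent. The second is a composite of glucose control and GI tolerability.
- **Sets and test.** "In the FAS and PPS populations, the percentages of patients achieving the therapeutic goals will be analyzed and compared between treatment groups", by the chi-square test. The same section makes the FAS the primary population for the change in HbA1c, but does not rank the two sets for the responder goals.
- **PPS membership.** "The per-protocol set (PPS) will include ITT patients completing at least 22 weeks of treatment". The one exception for early stoppers is "those who discontinued the study due to a poor therapeutic response (FPG >13.3 mmol/L [240 mg/dL]) after 12 weeks of treatment". Both routes also require no major deviation and a valid HbA1c within 7 days of the last dose.
- **GI stops.** Study design lists GI side effects among the adverse events that end treatment in either arm. The text after Table 2 adds: "Treatment will also be discontinued if the patient cannot tolerate the GI symptoms associated with a dose increase at visit 2". At visit 2, Group A stays on metformin 500 mg bid and Group B goes to 500 mg tid.
- **Expected direction.** Background describes metformin's GI effects as rising with dose and as a common reason for stopping.

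**The concern.** A patient taken off study drug before week 22 because of GI symptoms cannot have met a goal that requires no GI side effects. The result is known whatever the HbA1c. The PPS rule nevertheless takes this patient out of the denominator. The plan avoids the same problem for glycemic failure, by keeping poor-response stops after week 12, but not for the GI half of the composite.

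The loss is unlikely to be balanced. Only Group B's metformin is increased, so a larger share of Group B is expected to leave for GI reasons, and its PPS success rate rises more.

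The trial asks whether the combination gives equivalent glucose control with fewer adverse events, and this is the only listed efficacy goal that joins the two. Its PPS result would stand beside the FAS result with no stated order between them.

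**Working it through.** The plan gives no expected rate for this goal, so there is no figure of its own to reproduce.

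**Inputs from the article.** Total 3312, randomized 5:1: 3312 × 5/6 = 2760 in Group A and 3312/6 = 552 in Group B. On dropout, Sample size estimations says only "Allowing for a 20% dropout rate", with no split by arm or reason.

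**Assumptions.**
- GI stops before week 22 are 1% to 3% in A and 3% to 15% in B.
- The true success rate is 40%, with all treated patients in the denominator and GI stops counted as failures.
- No other PPS exclusions apply.
- The chi-square test is two-sided at 0.05; the article does not state the level for this goal.

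**Formula.** Let p be the true rate and g the share stopped for GI intolerance. All of g are failures, so removing them leaves the successes unchanged and shrinks the denominator: PPS rate = p/(1 − g).

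**One case in full (A 2%, B 10%, p = 40% in both arms).**
- A: 0.40/0.98 = 40.8%. B: 0.40/0.90 = 44.4%. Difference A − B = −3.6 points; the true difference is 0.
- PPS sizes: 2760 × 0.98 = 2704.8 and 552 × 0.90 = 496.8.
- Pooled rate: (1104 + 220.8)/3201.6 = 0.414.
- Standard error: √(0.414 × 0.586 × (1/2704.8 + 1/496.8)) = 2.4 points.
- The false difference is about 1.5 standard errors, and the test would be significant about 33% of the time.

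**All cases.** The last column takes a true 40% in A against 35% in B, a 5.0-point advantage for vildagliptin.

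| GI stops A/B | Patients removed A/B | PPS rate A/B, true 40% in both | A − B (true 0) | Chance of a significant test | A − B in PPS (true +5.0) |
|---|---|---|---|---|---|
| 1%/3% | 28/17 | 40.4%/41.2% | −0.8 | 6.5% | +4.3 |
| 1%/5% | 28/28 | 40.4%/42.1% | −1.7 | 11% | +3.6 |
| 2%/10% | 55/55 | 40.8%/44.4% | −3.6 | 33% | +1.9 |
| 3%/15% | 83/83 | 41.2%/47.1% | −5.8 | 65% | +0.1 |

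With a true 30% in both arms the false difference runs from 0.6 to 4.4 points; with 50%, from 1.0 to 7.3 points. Further PPS exclusions would shrink the sets and lower the chances of a significant test. If they fell equally on successes and failures, they would not remove the bias.

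**Same goal in the FAS.** A GI stopper who stays in the denominator is a failure by the goal's own wording, so the bias is 0.

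**The case against.** The strongest reply is that little depends on this. The goal is secondary and lies outside the described test sequence, the same comparison is made in the FAS, and a gap between the two sets would be visible. All of that stands, and it limits the weight of the point.

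Three stronger readings are tempting, and the article does not support them.

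- **That these patients are also lost from the FAS.** The article says "For assessment of missing primary efficacy variables, the last observation carried forward (LOCF) technique will be used" and gives no scoring rule for the responder goals. But the goal's wording already makes a GI stop a failure. Table 3 also requires the visit 5 assessments, HbA1c and adverse events included, at early withdrawal, so most such patients should have the post-baseline evaluation that FAS entry needs. A scoring rule for missing responder data is commonly left to the analysis plan, which is not shown.
- **That the tolerability difference is hidden.** The incidence of any GI event is compared separately by Fisher's exact test, and entry to the safety set needs only one dose and one later safety assessment. Patients with GI side effects who complete 22 weeks stay in the PPS and still fail the goal. Group B patients with GI symptoms at visit 3 may have the dose reduced and continue.
- **That most of the removed patients come from metformin.** GI side effects can end treatment in either arm. With 5:1 allocation, 1% of 2760 and 5% of 552 are both about 28 patients. What is expected to be larger in Group B is the share, and the share drives the bias.

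One further objection is partly right. The poor-response exception is not an exact precedent, since it applies only after week 12 and with a valid HbA1c close to the last dose. But a GI stop needs no HbA1c to be scored on this goal, so the reason to keep it is at least as strong.

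The reply that the analysis plan may settle the matter does not meet the PPS point. The article itself defines the set and assigns the goal to it, and an imputation rule cannot restore patients whom the set excludes.

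**Conclusion.** The point holds for the PPS comparison of this one secondary goal. A stated rule removes certain failures, probably a larger share of them from the metformin arm, and the resulting bias runs against vildagliptin. The direction rests on GI stopping being proportionately more frequent under up-titration, which the article's own Background and dosing scheme lead one to expect but do not quantify. The size rests wholly on assumed rates: about 0.8 to 5.8 points at a true 40% in both arms, which is minor at low GI stopping and enough to cancel a true 5-point advantage at 3% against 15%. The FAS result, the primary non-inferiority conclusion and the separate GI incidence test are not affected.

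**What to change.** In Data analysis, name the FAS as the analysis set for the composite of HbA1c at or below 6.5% with no GI side effects. If a PPS version is kept, do one of the following:

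- keep patients who stopped study drug for GI intolerance in it and count them as failures, without requiring an HbA1c within 7 days of the last dose, since their result does not depend on it; or
- label the PPS version as supportive only and state that it leaves out GI-intolerance stops.

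No change to the HbA1c-only goals follows from this point.

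The cost is a sentence or two. No new data are needed, because the reason for discontinuation is already recorded in the case report form. The downside is a slightly lower reported success rate where GI stops are kept as failures.
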